## 6. Data Management and Quality Control

During the study period, we will collect data from electronic medical records. All patients undergoing endovascular procedures during the study period will be selected and included if they meet the inclusion criteria. All the data obtained will be anonymized and a consecutive participation number will be assigned as the inclusion process is executed. Once this process has been accomplished, statistical analysis will be performed. These activities will be supervised by the coordinating researcher of the study.

## 7. Patient and Public Involvement

Patients and/or the public were not involved in the design, conduct, reporting, or dissemination plans of this research.

## 8. Ethics, Approval and Dissemination

The treatment of patient data within the framework of this study will comply with the provisions of current legal regulations at the national and European level: Organic Law 3/2018 on the Protection of Personal Data and Guarantee of Digital Rights, and Regulation (EU) 2016/679 General Data Protection. Patient data will be coded using a numerical code for the purposes of this study, eliminating any identifying or identifiable data. The research file will be kept in an electronic directory of the center, with restricted access, under the supervision of Information Systems of the Hospital Universitari de Bellvitge.

The researcher agrees to disseminate and publish the results in accordance with current legislation and the Declaration of Helsinki (Fortaleza, 2013). In the publications and other means of disseminating the results, the anonymity of the patients will be maintained.

Any written or oral communication of the research results must be approved by the research coordinating investigator and, where appropriate, in collaboration with the associated scientists.

All data transferred between sites will be encrypted, and no individual will be identifiable from the stored data. Identifiable patient information will be stored in a locked cabinet, accessible only by research members at the site of the data collection. The clean database file will be anonymized and kept for 25 years.

## 9. Discussion

X-ray exposure has been studied in recent years, especially during endovascular exclusion of abdominal aortic aneurysms [24,25,26]. Of particular interest is the comparison between the doses used depending on the equipment used: fixed or mobile. The scarcity of studies that analyze radiation based on the type of procedure and its complexity persists. For all these reasons, we believe that the present study can contribute knowledge in little-explored areas, such as the analysis of the radiation dose considering the level of complexity of the procedures on endovascular surgery.

The increasing number of endovascular procedures performed nowadays determines a greater exposure to ionizing radiation by patients and professionals during diagnosis, treatment, or follow-up. X-rays and their possible harmful effect remain subjects of study. With this study, we plan to analyze the radiation dose during the endovascular procedures performed in a Vascular Surgery department.

Radiation dose monitoring in endovascular surgery allows the analysis of X-ray exposure of patients and healthcare professionals involved. Additionally, strategies could be developed to lower the absorbed dose and the yearly number of procedures with high levels of dose area product and air kerma [8,22,26].

## 10. Conclusions

In conclusion, the analysis of radiation data of endovascular procedures is essential to detect which imaging systems and procedures involve higher doses. This is an observational and prospective study that attempts to examine the radiation dosage in two distinct imaging systems, using a classification of complexity levels in order to achieve a reliable comparison.

## Figures and Tables

**Table 1 mps-06-00049-t001:** Description of other radiation dose measures.

Parameters	Description
**Air kerma (AK)**	Represents the kinetic energy released per unit mass when an X-ray beam travels through air. The unit is milliGrays (mGy). It will be recorded by the system.
**Air-kerma area product (KAP or dose area product, DAP)**	The KAP is the product of two factors, namely the air kerma free in the air over the area of the X-ray beam in a plane perpendicular to the beam axis.
**Fluoroscopy time (FT)**	The time of exposure to X-ray, expressed in seconds. Fluoroscopy is a radiographic technique used for the visualization of anatomical structures in motion that allows guiding different diagnostic and therapeutic procedures in real-time. The unit is seconds. It will be recorded by the system.
**Contrast volume**	The total volume of contrast injected into the patient during the procedure. The unit is milliliter (mL).
**Body mass index (BMI)**	The measure of the weight compared to the height. The total amount of dose delivered will be correlated with patient size and weight.
**Number of DSA series**	The total number of digital subtraction series.
**Procedure time**	The total time interval from the start and end of the procedures, recorded in minutes (min).
**Type of anesthesia**	Described as general or loco-regional.

**Table 2 mps-06-00049-t002:** List of endovascular procedures.

Endovascular Procedures	Description
(1) Endovascular exclusion of abdominal aortic aneurysm	Placement of stent graft for internal lining of the aorta to exclude abdominal aneurysm.
(2) Endovascular exclusion of thoracic aorta	Placement of stent graft for internal lining of the thoracic aorta to exclude aneurysm, dissection, intramural hematoma, penetrating aortic ulcer or traumatic aortic injury.
(3) Endovascular exclusion of thoracoabdominal aortic aneurysm	Placement of stent graft for internal lining of the aorta to exclude thoraco-abdominal aneurysm.
(4) Endoleaks repair	Procedures that involve repairing blood flow between the graft and the aneurysm.
(5) Iliac percutaneous transluminal angioplasty or recanalization	Flow restoration procedure of the iliac sector through dilation with balloon catheter, with or without stent placement.
(6) Iliac stent	Stent placement in the iliac sector.
(7) Femoropopliteal percutaneous transluminal angioplasty or recanalization	Flow restoration procedure of femoropopliteal sector with or without stent placement.
(8) Femoropopliteal stent	Stent placement in the femoropopliteal sector.
(9) Infrapopliteal percutaneous transluminal angioplasty	Flow restoration procedure of the infrapopliteal sector through dilation with balloon catheter.

**Table 3 mps-06-00049-t003:** Complexity levels of endovascular procedures.

Low Complexity
A. Angioplasty of any territory
1. Arterial puncture without incidents 2. The guide passes easily without requiring specific material changes or multiple attempts 3. Absence of complication in the final angiogram 4. No arterial access complications
**Medium Complexity** (if any of the following are true)
A. Angioplasty of any territory
1. Difficult arterial puncture but achievable 2. Contralateral approach 3. Laborious recanalization of the stenosis/occlusion requiring one of the following conditions: guidewire/catheter changes collaboration of a second vascular surgeon 4. Presence (or not) of residual dissection on final angiogram 5. Presence (or not) of complications of arterial access
B. Angioplasty and stenting of any territory: whenever a stent implant is required, it will be of medium complexity (at least)—TASC A/B (aortoiliac), GLASS 1–2.
C. Recanalization of any territory—TASC A/B (aortoiliac)
D. Aortic endoprosthesis
1. An arterial approach without incidents (open or percutaneous) 2. Non-hostile anatomy (neck length > 15 mm and/or neck diameter < 32 mm, length of iliac arteries > 15 mm and/or diameter <20 mm) 3. Implantation of the device without incident 4. Easy catheterization of the contralateral limb 5. Absence of endoleaks in the final angiographic control (except type II)

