The decision to use a fixed C-arm or a mobile C-arm in our facility is made based on the availability of the X-ray equipment and the schedule of the procedures. In this study, we focus on arterial procedures: endovascular treatment of thoracic, abdominal, and thoracoabdominal aortic aneurysms, and procedures involving the revascularization of lower limbs.

Notwithstanding the widespread use of X-ray imaging units, there are a lack of published data about the impact of radiation exposure, and fixed C-arms are still related to higher radiation exposure [11,12,13].

The collection and subsequent analysis of radiological, clinical, and procedural parameters would identify opportunities for improvement in workflow and biosafety.

The results of this study may act as a springboard for further research on the comparison of radiation exposure between both X-ray equipment types according to complexity stratification of endovascular procedures. The identification of procedures that involve higher doses of radiation will allow the development of strategies to enhance safety in operating rooms where radiation exposure is involved.

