### 2.2. Secondary Objectives

The secondary objectives are: (1) Define the diagnostic reference radiation doses (DRLs) according to the procedure and its complexity, following the guidelines of the International Commission of Radiation Protection (ICRP) [14,15,16,17,18,19] and the European Council Directive 2013/59/EURATOM [20]. (2) Compare the dosimetric information provided in the dose reports of each procedure, based on the degree of complexity, in view of the implemented radiation protection measures. (3) Analyze the contrast dose used during the procedures on each device. (4) Associate the radiation dose of endovascular procedures with patients’ body mass index.

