### 3.4. Inclusion Criteria

All patients of ≥18 years agree to participate in the study by signing informed consent for one of the following procedures: (a) elective endovascular procedures for exclusion of thoracic and/or abdominal aortic aneurysm; (b) elective endovascular procedures for lower limb-threatening ischemia.

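### The dose–BMI association (secondary objective 4) is fixed as a plain correlation without separation or adjustment by anatomical territory, so it can be diluted or confounded by procedure type

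*Protocol article*

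**What the plan says.** Section 2.2 of the protocol article gives objective 4 as "Associate the radiation dose of endovascular procedures with patients’ body mass index". The BMI row of Table 1 adds the method: "The total amount of dose delivered will be correlated with patient size and weight". Neither place names a stratum, a covariate or which dose quantity is meant (peak skin dose, air kerma or KAP).

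The other secondary objectives do carry a qualifier:
- Objective 1 is "Define the diagnostic reference radiation doses (DRLs) according to the procedure and its complexity".
- Objective 2 is "based on the degree of complexity, in view of the implemented radiation protection measures".
- Objective 3 looks at contrast separately on each device.

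The Introduction describes the scope as "endovascular treatment of thoracic, abdominal, and thoracoabdominal aortic aneurysms, and procedures involving the revascularization of lower limbs". Section 3.4 admits "elective endovascular procedures for exclusion of thoracic and/or abdominal aortic aneurysm" and "elective endovascular procedures for lower limb-threatening ischemia". Table 2 lists aortic, endoleak, iliac, femoropopliteal and infrapopliteal procedures. On associations, Section 5.2 has only a one-line promise of what it calls partnership studies. Procedure type is recorded (Section 3.8.2), and so is the device (Section 3.8.1).

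**The concern.** In some of these procedures the beam crosses the trunk and in others the leg. BMI is a plausible marker of tissue thickness in the beam for the trunk, and probably a weaker one for femoropopliteal or infrapopliteal work. The study also starts from the premise that dose depends on procedure. A single correlation of dose with body size over such a mix has three weaknesses:

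- **Averaging.** If the BMI effect differs by territory, the result describes neither territory.
- **Dilution.** A dose gap between territories adds variance unrelated to BMI and lowers the correlation.
- **Confounding.** If mean BMI also differs between procedure groups, part of the dose gap is credited to BMI, in either direction.

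The study's main stratifier does not solve this. In Table 3 the low level covers angioplasty wherever it is done, and the medium and high levels hold both peripheral procedures and aortic endoprostheses. At stake is the interpretability of objective 4, in particular for the procedures in which body size may matter most.

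**Working it through.** The article states no figure for the BMI association, so there is none to reproduce. What follows tests the mechanism.

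**From the article.** 150 to 200 procedures a year (Section 5.1) over 30 months (Section 3.2) gives 150 × 2.5 = 375 to 200 × 2.5 = 500 procedures. The significance level is 0.05 (Section 5.2), taken here as two-sided.

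**Assumed, because the article gives no dose or BMI data.** *p* is the share of trunk (aortic or iliac) procedures; *s* = 4.5 is the within-territory SD of BMI; *m* is mean BMI in trunk minus leg patients; *R* is the trunk/leg dose ratio at a reference BMI; *b*T and *b*L are the slopes of ln dose per BMI unit; σ is the residual SD of ln dose.

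**Formulas.** The gap in mean ln dose is g = ln R + (bT + bL)·m/2, with the reference BMI midway between the two group means. Then

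- cov = [p·bT + (1−p)·bL]·s² + p(1−p)·m·g
- var(BMI) = s² + p(1−p)·m²
- var(ln dose) = [p·bT² + (1−p)·bL²]·s² + σ² + p(1−p)·g²
- pooled slope = cov / var(BMI); pooled r = cov / √[var(BMI)·var(ln dose)]

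**Setting 1: same slope in both territories** (b = 0.05, σ = 0.8). The within-territory r is 0.05 × 4.5 / √(0.225² + 0.8²) = 0.225/0.831 = 0.27.

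Worked case with p = 0.5, R = 5, m = −2:
- g = 1.609 − 0.100 = 1.509
- cov = 1.0125 − 0.7547 = 0.258
- var(BMI) = 20.25 + 1 = 21.25
- var(ln dose) = 0.0506 + 0.64 + 0.5696 = 1.260
- slope = 0.258/21.25 = 0.012; r = 0.258/√(21.25 × 1.260) = 0.05

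By Fisher's z, power for r = 0.05 is 16% at 375 procedures and 20% at 500. For r = 0.27 it is close to 100% at either size.

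Over p = 0.3 to 0.5 and R = 3 to 10:

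| m | Pooled slope (true 0.050) | Pooled r (within 0.27) |
|---|---|---|
| −2 | −0.004 to 0.028 | −0.01 to 0.14 |
| 0 | 0.050 | 0.16 to 0.23 |
| +2 | 0.072 to 0.104 | 0.32 to 0.34 |

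With equal mean BMI the slope is unbiased and only r shrinks. The sign reverses only if trunk patients are leaner by more than about 1.8 to 2.2 units at R = 10, 2.8 to 3.3 at R = 5, or 4.7 to 6.1 at R = 3.

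**Setting 2: different slopes** (bT = 0.07, bL = 0.01, σ = 0.7, p = 0.5). Within-territory r is 0.41 for trunk and 0.06 for leg. Pooled slope / r:

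| m | R = 3 | R = 5 | R = 10 |
|---|---|---|---|
| −2 | 0.014 / 0.07 | 0.002 / 0.01 | −0.014 / −0.05 |
| 0 | 0.040 / 0.20 | 0.040 / 0.17 | 0.040 / 0.13 |
| +2 | 0.066 / 0.32 | 0.078 / 0.32 | 0.094 / 0.31 |

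At m = 0 the slope is the plain average, (0.07 + 0.01)/2 = 0.04, whatever the dose gap. It is unconfounded but true of neither territory. Power for those three correlations at 375 to 500 procedures is about 97–99%, 90–96% and 72–84%.

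**If BMI has no effect in the leg** (bT = 0.05, bL = 0, σ = 0.8, p = 0.5, R = 5), pooled r is 0.10 at m = 0, 0.02 at m = −1 and −0.05 at m = −2, against 0.27 within trunk procedures.

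**The case against.** The strongest reply is that the article never says the correlation will be pooled. The Table 1 sentence sits in a description of variables, and strata, covariates and transformation for a secondary association are commonly left to a full protocol or analysis plan, neither of which is shown. This stands in part: pooling is the plain reading, not a stated rule. But the article does name a method, a correlation of total dose with body size, and leaves objective 4 alone among the four without a qualifier. The point is about that stated choice, not about missing detail.

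Second, a reader might infer that the pooled result mainly reflects which disease the patient has. The article does not support this. It needs a BMI difference between procedure groups, and no BMI figures are given. Disease and region do not coincide either: iliac revascularisation is trunk work but would enter under the limb-ischemia criterion.

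Third, a reader might infer that a real BMI effect will be missed or its sign reversed. With equal mean BMI, setting 2 still leaves 72–99% power to detect some association. Reversal needs trunk patients to be leaner, combined with a large dose gap or a very weak leg effect. Inflation is just as possible if they are heavier. It would also be unfair to take the trunk-only r of 0.41 as the true value for an objective that covers all endovascular procedures.

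Finally, this is one secondary objective of an observational study, and no data are lost, since territory can still be brought in at analysis. That is correct and limits the weight of the point.

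**Conclusion.** The concern holds in a limited form. As written, objective 4 rests on an unadjusted correlation in a cohort that mixes aortic and iliac with infrainguinal procedures, and complexity strata would not separate them. Such a correlation averages possibly different BMI effects, is diluted by any dose gap between procedures, and is confounded if BMI differs between procedure groups. Confounding could hide the association, inflate it or, in extreme cases, reverse it.

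The actual size cannot be known from the article. In setting 1 with p = 0.5 and R = 5, a true 5.1% increase per BMI unit (e^0.05 − 1) would read as 1.2% (e^0.012 − 1) with trunk patients 2 units leaner, or 9.2% (e^0.088 − 1) with them 2 units heavier. With equal mean BMI only the correlation changes, from 0.27 to 0.19. All of these rest on assumed slopes, spreads, shares and dose ratios. The primary comparison of the two imaging systems is not affected.

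**What to change.** In objective 4 and the BMI row of Table 1:

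- Name the dose metric to be related to BMI.
- Estimate the association on log dose, with procedure type (or territory: aortic/iliac versus infrainguinal) and device in the model.
- Include a BMI-by-territory term, or give separate estimates for each territory.
- Report percent change in dose per BMI unit with a 95% CI.
- Label any correlation over all procedures as descriptive.

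Complexity level should not stand in for territory. The change is wording only, as BMI, procedure type and device are already collected. The cost is some precision: with an equal split, each territory-specific interval is about √2 = 1.41 times as wide as that of a single adjusted slope over all procedures.

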## 2. Aims and Objectives

### 2.1. Primary Objective

This study aims to analyze radiation used during endovascular procedures according to complexity, comparing a mobile X-ray system (Philips Zenition 70 ^®^) with a hybrid room (Philips Azurion ^®^).

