#### 3.8.3. Complexity Levels

To obtain a reliable comparison across endovascular procedures, we have devised a framework for categorizing procedures on three levels of complexity considering type of surgery. In aortic procedures, the degree of complexity depends on arterial access, aortic neck anatomy, contralateral leg catheterization and iliac anatomy. For peripheral artery procedures we consider the Global Limb Anatomic Staging System (GLASS) (infrainguinal chronic limb threatening ischemia) [24], the Trans-Atlantic Inter-Society Consensus Document on Management of Peripheral Arterial Disease classification (TASC II) (aortoiliac lesion) [25], the possibility of recanalization, and the occurrence of dissection and/or thrombosis (Table 3).

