**High Complexity**
A. Angioplasty/stent of any territory
1. Difficult arterial puncture requiring a change to open approach or arterialficult arterial puncture requiring a change to open approach or arterial access 2. Access from upper limb (UL) 3. Laborious recanalization of the stenosis/occlusion requiring one of the following conditions: guidewire/catheter changes collaboration of a second vascular surgeon retrograde puncture 4. Final angiogram with dissection/thrombosis requiring extra procedures (for example thrombectomy) 5. Presence of complications of arterial access
B. Recanalization of any territory
1. Difficult puncture requiring a change of approach point/open approach 2. Access from UL 3. Recanalization of an entire arterial axis (iliac, femoral and/or distal trunks)—TASC C/D (aorto-iliac), GLASS 3. 4. Laborious recanalization of the stenosis/occlusion requiring one of the following conditions: guidewire/catheter changes collaboration of a second vascular surgeon retrograde puncture 5. Final angiogram with dissection/thrombosis requiring extra procedures (for example thrombectomy) 6. Presence of complications of arterial access 7. Despite multiple attempts, it is not possible to recanalize the occlusion
C. Aortic endoprosthesis
1. Complication of the arterial access (open or percutaneous) 2. Hostile anatomy (neck length < 15 mm and/or neck diameter > 32 mm, length of iliac arteries < 15 mm and/or diameter > 20 mm) 3. Complex catheterization of the contralateral limb requiring extra procedures (for example, single-loop snare) 4. Additional procedures for endoleak treatment (such as central cuff extension or additional iliac limb) 5. Additional procedures as embolization of inferior mesenteric/internal iliac artery, placement of endo-anchor, etc. 6. Chimney or snorkel technique 7. Fenestrated or branched aortic endograft 8. Iliac branch

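### Table 3's complexity levels, which stratify the device comparison and the reference levels, are not mutually exclusive as written

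*Protocol article*

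**What the plan says.** Section 2.1 makes complexity part of the primary objective: "This study aims to analyze radiation used during endovascular procedures according to complexity", comparing a mobile system with a hybrid room. Section 2.2 sets diagnostic reference levels by procedure and complexity. Section 3.8.3 says "we have devised a framework for categorizing procedures on three levels of complexity considering type of surgery", so that procedures can be compared reliably.

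Table 3 defines the levels.

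- **Low** covers angioplasty only. Its list begins "1. Arterial puncture without incidents 2. The guide passes easily without requiring specific material changes or multiple attempts" and goes on to require no complication on the final angiogram or at the access site. No connective is printed.
- **Medium** applies "if any of the following are true". Angioplasty items A.4 and A.5 are "4. Presence (or not) of residual dissection on final angiogram 5. Presence (or not) of complications of arterial access". Item A.3 is laborious recanalization with a guidewire or catheter change or a second surgeon. Item D.2, for aortic endografts, describes non-hostile anatomy, starting "neck length > 15 mm and/or neck diameter < 32 mm".
- **High** repeats the laborious-recanalization item at A.3 and B.4, "requiring one of the following conditions: guidewire/catheter changes collaboration of a second vascular surgeon retrograde puncture", and lists access complications at A.5 and B.6. Item C.2 describes hostile anatomy, starting "neck length < 15 mm and/or neck diameter > 32 mm". No connective is printed.

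The only floor rule is for stents, which are at least Medium. There is no general rule for a case that meets two levels.

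**The concern.** Rooms are assigned by availability, not at random (Sections 3.1 and 4), and complexity is the case-mix control that the article names for the device comparison. If one procedure can meet two levels and nothing says which prevails, two people applying the same table to the same case can place it differently. Doses by level, the mobile-versus-hybrid contrast within a level and the reference levels then depend on unstated choices and cannot be reproduced from the published criteria.

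**Working it through.** The plan gives no figure to reproduce here. The check is of logic.

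**Angioplasty without stent.** Inputs from Table 3: puncture (easy, difficult, approach changed), contralateral approach, upper-limb access, laborious recanalization, retrograde puncture, dissection (none, residual, needing extra procedures) and access complication. That gives 3 × 2 × 2 × 2 × 2 × 3 × 2 = 288 profiles. Low is read as all items, Medium as any item (as printed) and High as any item (assumed). Retrograde puncture is counted as meeting High A.3.

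| Reading of Medium A.4 and A.5 | Low only | Low and Medium | Medium and High | Exactly one level | No level |
|---|---|---|---|---|---|
| Literal (always true) | 0 | 4 | 280 | 6 | 0 |
| Presence only | 1 | 2 | 273 | 13 | 0 |
| Irrelevant (deleted) | 1 | 2 | 234 | 51 | 1 |

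A profile that meets all three levels is counted in both overlap columns.

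- Literal reading: Low holds for 1 × 2 × 2 × 1 × 1 × 1 × 1 = 4 profiles, because contralateral and upper-limb access are left free. All 4 also meet Medium.
- Items deleted: the 2 profiles that are both Low and Medium have a contralateral approach, which Medium A.2 lists and Low does not exclude. The profile with no level has residual dissection and nothing else.
- Items deleted: laborious recanalization is present in 288 / 2 = 144 profiles, and each meets both Medium A.3 and High A.3. The other 234 − 144 = 90 overlaps combine a Medium item with a different High item. A highest-level rule alone would settle those 90. Applied to the 144, it would send all of them to High and leave Medium A.3 with no effect.

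**Aortic anatomy.** Four features (neck length, neck diameter, iliac length, iliac diameter), each favourable or hostile, give 2⁴ = 16 patterns. 'And/or' is read as 'or' within each pair, except in the last line.

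- Neck and iliac pairs joined by 'and' for non-hostile and by 'or' for hostile: non-hostile 3 × 3 = 9, hostile 16 − 1 = 15, both 9 − 1 = 8.
- 'And' between pairs in both definitions: both 2 × 2 = 4.
- 'Or' between pairs in both definitions: both 16 − 2 = 14.
- All four features required for non-hostile, any one enough for hostile: both 0.

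Example: a neck 10 mm long and 28 mm wide meets D.2 on diameter (28 < 32) and C.2 on length (10 < 15).

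Separately, the 'any' header of Medium also governs section D. A hostile neck with easy contralateral catheterization therefore meets Medium D.4 and High C.2.

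**Coverage.** Endoleak repair is a procedure type in Table 2 (row 4). In Table 3, treatment of an endoleak appears only as an additional procedure under aortic endoprosthesis (High C.4).

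**The case against.** The fairest defence is that Medium A.4 and A.5 mean 'regardless of', in contrast to the Low items that require absence, and that readers will assign the highest level met, as the stent floor suggests. The full protocol may say so.

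The first part is plausible, and it limits what can be claimed. A reader might infer that the Low stratum is lost. That needs both the literal reading and a rule that the higher level prevails, and the article states no such rule. Even so, the duplicated laborious-recanalization item and the contralateral overlap survive the generous reading. The table is published as the classification, so this is a fault in stated criteria and not an omission.

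Other stronger inferences also fail:

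- That half of aortic cases are ambiguous: 8 of 16 is one reading of the punctuation, and patterns are not patients.
- That infrainguinal recanalization at GLASS 1–2 has no level: Medium C covers recanalization of any territory, and its TASC grade is tagged to aortoiliac disease. Only the GLASS label is missing.
- That a neck of exactly 15 mm or 32 mm is never classified: with 'and/or' read as 'or', a neck of 15 mm and 28 mm is non-hostile on diameter. Setting the iliac features aside, only a neck at both cut-offs is then left out.
- That levels are assigned by people who know the room and the dose: the article does not say who assigns them or what they know.

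**Conclusion.** The point holds as a defect of wording in the stratifier of the primary objective. Four parts stand: always-true items in an any-of list if read literally; the same laborious-recanalization conditions in Medium and High on every reading; anatomy definitions that are not complementary when 'and/or' is read as 'or'; and no general precedence rule. Stand-alone endoleak repair also lacks a clear level.

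On the generous reading, 234 of 288 angioplasty profiles still meet both Medium and High, 144 of them through the duplicated item. Aortic overlap runs from 0 to 14 of 16 patterns. These figures assume that any single High item is enough, and they say nothing about how many patients are affected; the article gives no expected share per level. The documents do not show that Low will be empty or that assignment has been biased.

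**What to change.** Reword Table 3:

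- State the order: High if any High item is met; otherwise Medium if any Medium item is met; otherwise Low.
- Replace Medium A.4 with residual dissection not requiring extra procedures. Simply deleting it would let such a case fall to Low, against Low item 3. Delete A.5, leaving access complications in High only.
- List each laborious-recanalization condition in one level only, for example guidewire or catheter change and second surgeon in Medium, retrograde puncture in High.
- Require all Medium D items, define non-hostile as no hostile criterion met, and assign values at the cut-offs to one side. Confine the final step to angioplasty, because Low lists nothing else, and name the level for an aortic case that misses a D item without meeting a High item.
- Name the level for stand-alone endoleak repair.

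With that example allocation, the 288 angioplasty profiles each get one level. Those with no High item number 2 × 2 × 1 × 2 × 1 × 2 × 1 = 16. One of these is Low and 15 are Medium; the remaining 288 − 16 = 272 are High.

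Re-apply the corrected table to all cases, blind to dose and before the device comparison. The cost is a re-coding pass, with chart review where an operative detail was not recorded item by item. No new patients or dose measurements are needed.
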